##### Adaptations and safety considerations

4.9.2.5

Standardized adaptation strategies will be applied consistently across both the experimental and control groups. Sessions will be modified or temporarily suspended on an individual basis when altered physiological parameters will be detected. Participants presenting resting blood pressure values >180/110 mmHg at session onset will be advised to regulate blood pressure pharmacologically and to perform exercise at moderate intensity. Participation will be suspended if systolic blood pressure exceeded 220 mmHg and/or diastolic blood pressure exceeded 105 mmHg, or in cases of hypotension during the session (38, 39).

For participants with diabetes, exercise will be avoided if pre-session blood glucose levels will be <90 mg/dL or >250 mg/dL (40). These glucose thresholds will be based on participants’ routine home self-monitoring of capillary blood glucose, as recommended in standard diabetes care. At the beginning of each training day, participants will be asked to report whether their most recent home reading falls within a safe range for exercise. On-site screening will include only blood pressure and heart rate measurements.

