### Participant recruitment

4.4

An open invitation will be extended to all adult women from the Huichacura-Cayuqueo Indigenous Community in the municipality of Padre Las Casas who meet the established eligibility criteria. Participant recruitment will be conducted through in-person informational meetings held at the community headquarters, complemented by digital dissemination coordinated in collaboration with the community leadership. Eligible participants will include sedentary adult Mapuche women (30, 31) with overweight or obesity and medically controlled cardiometabolic conditions, as verified through documented medical diagnoses, routine clinical follow-ups, and prescribed treatments provided by their respective primary health care centers. Participants must also demonstrate the physical ability to safely engage in moderate-intensity group exercise without assistance and have sufficient availability to attend the scheduled intervention sessions.

Individuals with medical conditions that contraindicate participation in group physical activity, including neurological events such as stroke or acute and chronic respiratory diseases, will be excluded. Detailed inclusion and exclusion criteria are presented in Table 1.

**Table 1 tab1:** Inclusion and exclusion criteria.

Inclusion criteria	Exclusion criteria
Be a woman aged 18 to 65 years.	To have organic pathologies that prevent physical activity, such as stroke, acute or chronic respiratory diseases.
Having a high level of sedentary lifestyle (more than 4 h per day) (30).	To have suffered a recent acute myocardial infarction (in the last 3 months).
To have a diagnosis of malnutrition due to overweight or obesity (based on BMI).	To have a cardiovascular pathology that prevents group physical activity.
If suffering from chronic diseases diagnosed by a doctor, such as diabetes, hypertension, or dyslipidemia, these must be properly controlled (medication use and corresponding medical checkups). with stable treatment for ≥3 months, including no recent changes in medication, no acute exacerbations, and ongoing clinical follow-up.	Having uncontrolled hypertension or diabetes mellitus, defined as lacking medical or pharmacological treatment, lacking clinical follow-up, or presenting clinical values that contraindicate participation in group exercise.

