Be willing to exercise and have time available between July and September 2024 (3 sessions per week, one hour each).	Neurological, respiratory, or systemic diseases that impair the ability to perform exercise (e.g., stroke, severe chronic respiratory disease).
To have time available for an evaluation before the intervention program in July and another at the end of the program in October (each lasting approximately 2 h).	Participate in another physical exercise program during the duration of the project.
Belong to the Huichacura Cayuqueo Indigenous Community.	Use of active obesity treatments, including pharmacological therapy for weight loss (e.g., naltrexone/bupropion or agents associated with significant gastrointestinal or exercise-limiting side effects) or bariatric surgery.
Demonstrate the ability to safely perform moderate-intensity exercise, confirmed through baseline clinical screening and a submaximal 3 × 1-min step test without adverse symptoms.	Not want to participate and not sign the consent form.
Be responsible with the schedules set for the evaluation and intervention.	

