##### Procedures

4.9.2.1

At the start of each session, participants’ blood pressure and heart rate will be measured to ensure safe participation in physical activity. Each session followed a standardized structure (Table 2). Although the intervention targets Mapuche women, traditional Mapuche ceremonial dances will not be incorporated due to their spiritual and ritual significance. Instead, Fit-Folk’s cultural adaptation is reflected in: (a) the use of folk and popular dance styles widely practiced in rural southern Chile, such as the cueca, rancheras, and cumbia, which are familiar and culturally significant to community members; and (b) the incorporation of deeply structured cultural elements, such as coordination with the Huichacura-Cayuqueo Indigenous Community, an all-female group format, culturally safe communication, and community-agreed norms. This approach ensures cultural relevance while maintaining respect for Mapuche ceremonial traditions.

**Table 2 tab2:** Structure of a Fit-Folk cardiovascular dance class.

Phase	Duration	Activity description	Intensity (Borg)	Dance styles	Country/folklore
Warm-up	8–10 min (2 to 3 songs)	Slow and progressive movements including joint mobility, basic dance steps, and dynamic stretching, aimed at increasing joint range of motion, body temperature, and cardiorespiratory activation.	Moderate, Borg 3–4	Huayno; Nicaraguan full-rhythm dances	CL and PE
Main development	35–40 min (14 to 16 songs)	The main phase of the session, characterized by higher-intensity rhythms and movements. Participants replicate Latin American folk choreographies guided by the instructor, emphasizing continuous movement and aerobic demand.	Moderate to Intense, Borg 5–9	Moderate-intensity dances: Tumbe; Afro-descendant Chilean rhythms from Arica; Colombian cumbia; Southern Chilean rancheras; Afrosaya (Bolivia); Chilean cueca. High-intensity dances: Tinkus; Forró (Brazil); Caporal; El Rin (Chile); Merengue.	BO, BR, CL, CO and PA
Cool-down/return to calm	8–10 min (2 to 3 songs)	Gradual reduction of movement intensity using slower dance steps, followed by static stretching to promote relaxation and recovery.	Low, Borg 1–3	Morenada; Venezuelan gaita; Peruvian waltz.	BO PE and VE

Borg, Borg rating of perceived exertion; BO, Bolivia; BR, Brazil; CL, Chile; CO, Colombia; PA, Panama; PE, Peru; VE, Venezuela.

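### The diastolic blood-pressure limits in section 4.9.2.5 run backwards: moderate exercise is advised above 180/110 mmHg, but participation is suspended above a diastolic of 105 mmHg

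*Protocol article*

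**What the plan says.** Section 4.9.2.5 (Adaptations and safety considerations) opens with a general rule: "Sessions will be modified or temporarily suspended on an individual basis when altered physiological parameters will be detected". It covers both arms: "Standardized adaptation strategies will be applied consistently across both the experimental and control groups". Two numerical rules follow in adjacent sentences.

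- Advice rule. Participants with "resting blood pressure values >180/110 mmHg at session onset will be advised to regulate blood pressure pharmacologically and to perform exercise at moderate intensity".
- Suspension rule. "Participation will be suspended if systolic blood pressure exceeded 220 mmHg and/or diastolic blood pressure exceeded 105 mmHg". The same sentence then adds low pressure as a further ground: "or in cases of hypotension during the session".

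The procedures section for the dance arm (4.9.2.1) places the safety check at the start of each session, when "blood pressure and heart rate will be measured to ensure safe participation in physical activity". Section 4.15.3 records blood pressure immediately before and at the end of a session. Table 1 excludes uncontrolled hypertension, defined by absent treatment, absent follow-up, or "presenting clinical values that contraindicate participation in group exercise". It also asks that participants "have time available between July and September 2024".

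**The concern.** A caution limit should be reached before a stopping limit. Here that holds for systolic pressure and fails for diastolic pressure. The same onset reading can lead to advice to exercise at moderate intensity and to suspension, and the text does not say which governs.

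What is at stake is participant safety. Women with treated hypertension may enter. By 4.9.2.5, on-site screening consists only of blood pressure and heart rate, so this is the on-site screening rule that carries numbers. It applies at every session: 3 per week × 12 weeks = 36 sessions per participant. Those who apply it are a dance instructor and a physical education professional, who should not have to infer which sentence prevails. The promise of consistent application across arms also depends on a rule that gives one answer.

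**Working it through.** No sample-size, power or error-rate figure is involved. The check is a comparison of the two rules, component by component. All inputs come from 4.9.2.5.

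**Order of the limits (suspension limit minus advice limit)**

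- Systolic: 220 − 180 = +40 mmHg. The order is correct.
- Diastolic: 105 − 110 = −5 mmHg. The order is reversed.

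**Overlap.** Suspension applies if systolic > 220 or diastolic > 105. It is therefore avoided only if systolic ≤ 220 and diastolic ≤ 105. The notation >180/110 can be read in two ways.

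1. *Both components must be exceeded.* The advice covers systolic > 180 with diastolic > 110. Every such reading has diastolic > 105, so every one also meets suspension, and the advice never applies alone. With diastolic above 110 but systolic at or below 180 (for example 150/112), suspension applies alone and there is no conflict.
2. *Either component suffices.* The advice covers systolic > 180 or diastolic > 110. Every diastolic above 110 then meets both rules. The advice applies without suspension only at systolic 181–220 with diastolic ≤ 105.

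| Onset reading (mmHg) | Both components required | Either component suffices |
|---|---|---|
| 200/100 | neither rule | advice only |
| 150/107 | suspension only | suspension only |
| 190/107 | suspension only | advice and suspension |
| 150/112 | suspension only | advice and suspension |
| 190/112 | advice and suspension | advice and suspension |

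On both readings, no value with diastolic above 105 meets the advice rule without also meeting suspension. There is no diastolic band in which modified exercise is the sole instruction. One part of the overlap under reading 2, systolic above 220 with diastolic at or below 105, is ordinary escalation and does not come from the inversion.

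**What the 110 figure can still do.** The advice has two limbs: medication, and moderate exercise. Only the exercise limb conflicts with suspension. If suspension prevails, 110 can still separate those told to regulate their pressure from those not told. Under reading 1, 190/112 gets the medication advice and 190/107 does not. Under reading 2, 150/112 gets it and 150/107 does not.

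**Onset versus in-session.** Suppose the suspension limits apply only once exercise has begun. A participant admitted with a resting diastolic above 110 starts above the stop limit and could continue only if her diastolic fell by more than 5 mmHg. At a resting diastolic of 106–110 with systolic ≤ 180 the advice rule is silent, yet she too is already above the stop limit.

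**The case against.** The strongest defence combines two readings. The first sentence concerns resting pressure at onset. The second omits the word resting and ends with a reference to the session. A participant above 180/110 would then first bring her pressure down, next exercise moderately, and stop if she passed 220 or 105 while exercising. This is a natural reading and it reduces the conflict. Section 4.7, which has instructors monitor physiological responses continuously, makes in-session use plausible. It does not settle the matter: no re-measurement after treatment is stated, the reference to the session attaches most directly to hypotension, and a resting diastolic of 106–110 is still above the stop limit.

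A second defence is that suspension naturally overrides advice. That is reasonable, but the text does not say so, and the opening sentence names modification and suspension without ranking them.

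A third is that other safeguards exist. Table 1 requires treatment stable for at least 3 months, baseline clinical screening and a symptom-free step test. Section 4.7 requires confirmed clinical stability and individualised intensity. These make extreme readings less likely and bear on severity, but they do not correct the figures.

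A reader might infer more than the article supports:

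- *That the 110 limit has no function if suspension prevails.* It could still trigger the medication advice.
- *That 105, or 110, is known to be the slip.* The article does not show which figure is wrong.
- *That nobody with an onset diastolic above 105 should exercise that day.* That presumes 105 is right and rules out exercise after treatment, which the first sentence may intend.

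**Conclusion.** The inconsistency stands. The diastolic limits are inverted by 5 mmHg, nothing else in the article reconciles them, and no diastolic above 105 can receive the moderate-exercise advice without also meeting suspension. This holds however >180/110 is read. The size of the overlap does depend on that reading: it is the whole advice rule if both components are required, and everything except systolic 181–220 with diastolic ≤ 105 if either suffices.

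This is not a detail that an article would leave to a fuller document: both figures are printed and they disagree. The conclusion rests only on the printed figures and takes no view on which is clinically right. The article gives no frequency for such readings, and they are probably uncommon given the exclusions, screening and monitoring. The point should be fixed on safety grounds. It has no claimed effect on the primary outcome, sample size or analysis. If the sessions are complete, it becomes a reporting matter.

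**What to change.** In this order:

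1. Have the responsible clinician confirm or correct the diastolic figures so that the caution limit lies below the suspension limit.
2. Reword the two sentences to state which limits apply to resting pressure at onset and which during the session, and whether one or both components must be exceeded.
3. State that suspension prevails when both rules are met, and that moderate exercise is allowed only below the suspension limits.
4. State whether a participant may exercise the same day after treatment and a repeat reading.

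If the sessions are already complete, as the July–September 2024 dates in Table 1 suggest, report instead which limits were actually applied in each arm.

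The cost is one clinician check, two reworded sentences and a short instructor briefing, or one reporting sentence if the sessions are over.

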##### Modifications and adherence

4.9.2.6

Any protocol modifications will be documented in the intervention log and reported in the final manuscript. Attendance at each session will be recorded, and constant communication will be maintained between participants and instructors through a dedicated WhatsApp group.

##### Intervention fidelity

4.9.2.7

Session fidelity will be assessed using post-session satisfaction surveys. Additionally, digital questionnaires will be administered throughout the intervention to capture covariates related to behavioral changes and barriers associated with participation in Fit-Folk Cardiovascular Dance activities.

### Conventional physical exercise program

4.10

#### Title of the intervention and its justification

4.10.1

The control condition will consist of a group-based conventional physical exercise program combining resistance and cardiorespiratory training. This intervention was selected due to its documented effectiveness in improving anthropometric, metabolic, and cardiorespiratory outcomes (25, 41).

#### Materials and setting

4.10.2

Equipment included kettlebells (4, 6, and 8 kg), dumbbells (2 and 3 kg), suspension trainers, elastic resistance bands, medicine balls (3 and 5 kg), exercise mats, agility ladders, cones, amplification equipment, and supportive community infrastructure.

#### Procedures

4.10.3

Each session will be organized into structured blocks. The initial warm-up block included dynamic stretching (42), joint mobility exercises, movement-specific preparatory drills (43), and neuromuscular activation.

The primary training block will emphasize high neuromuscular demand exercises (e.g., squats, deadlifts, overhead presses, rows), with exercise selection based on planned movement patterns and load prescription tailored to training objectives. Resistance training intensity will be monitored using the OMNI-RES perceived exertion scale (44).

Next, a secondary resistance block will be performed, characterized by reduced intensity and volume. An auxiliary block will be then implemented, focusing on core strengthening (45), joint mobility, large-joint stability, and advanced technical movements.

The metabolic conditioning block incorporated interval-based methods targeting both cardiorespiratory and muscular systems, monitored using the speech test (46) and Borg scale (47), including high-intensity interval training (HIIT) protocols when appropriate (48). Sessions concluded with a cool-down phase consisting of breathing exercises, joint mobilization, and static stretching (49, 50).

#### Provider

4.10.4

Sessions will be delivered in person by a qualified physical education professional with experience in adult fitness training.

#### Format and location

4.10.5

Group size will be consistent with the experimental condition (11 participants per group), and all sessions will be held at the Huichacura-Cayuqueo community center.

#### Training structure and frequency

4.10.6

A full-body training approach (51) using mixed training methods (52) will be employed. The 12-week program will be divided into three mesocycles: anatomical adaptation/general strength (weeks 1–4), hypertrophy/general strength (weeks 5–8), and muscular endurance/general strength (weeks 9–12). Exercise selection and distribution will be based on fundamental movement patterns and upper- and lower-limb push–pull dynamics (53). Training frequency and session duration matched the experimental group (three sessions per week, ~60 min each) (54).

### Intervention duration

4.11

The intervention will be conducted over a three-month period. Figure 1 presents a flow diagram outlining participant inclusion, follow-up procedures, and the timing of baseline and post-intervention assessments of the study variables.

### Participant compliance and follow-up criteria

4.12

Participant adherence will be defined as attendance at ≥80% of the scheduled FCD or CPE sessions (55). Attendance will be documented at the start of each session using a standardized recording form. Primary analyses will follow the intention-to-treat principle. In addition, a per-protocol sensitivity analysis will be performed, restricted to participants who attended at least 80% of the intervention sessions.

### Analysis variables

4.13

In both study arms, assessments will be conducted at baseline and post-intervention to evaluate physical health parameters, health-related quality of life, motivation for physical activity, and perceived barriers to and benefits of exercise. Data will be collected using standardized case report forms and subsequently entered into a secure database incorporating quality control procedures, including range checks and automated alerts for missing or inconsistent values. All assessments will be performed by qualified health professionals who will remain blinded to group allocation. Prior to study initiation, outcome assessors will receive structured training to standardize measurement procedures and ensure consistent application of assessment protocols, thereby enhancing reliability and minimizing measurement bias (56).

All assessment activities will take place at the Huichacura-Cayuqueo community center, following a scheduled appointment system and in a facility designed to ensure participant privacy and appropriate environmental conditions, including controlled temperature and humidity. Blood samples will be collected and analyzed at an accredited laboratory within the municipality of Padre Las Casas, in accordance with institutional procedures. Participants will be instructed to observe a fasting period of at least 8 h and no more than 12 h prior to blood collection to ensure analytical accuracy.

### Main variables

4.14

#### Cardiorespiratory capacity

4.14.1

Cardiorespiratory fitness will be the primary outcome of the trial and will be assessed using the 3 × 1 Step Test (ST3 × 1), a validated protocol for estimating VO₂max in adults with cardiovascular risk factors (57). During the test, participants will repeatedly step up and down from a standardized platform (0.20 m in height) across three progressively demanding 1-min stages, each separated by a 1-min recovery period. Heart rate and blood pressure will be measured immediately upon test completion and again after one minute of recovery.

Test-derived estimates will be recorded and interpreted using age- and sex-specific normative reference values. Results falling below the established percentile thresholds will be classified as indicative of diminished cardiorespiratory fitness (58).

To ensure participant safety during the 3 × 1 Step Test, trained evaluators will monitor blood pressure and heart rate before the test, conduct continuous observation for signs of exercise intolerance during the protocol, and repeat cardiovascular measurements immediately after completion and during the recovery period. The test will be discontinued if any adverse symptoms occur, and participants exhibiting abnormal responses will be referred for clinical evaluation.

#### Strength

4.14.2

##### Upper extremity strength

4.14.2.1

Handgrip strength will be assessed using a calibrated hand dynamometer, which is a recognized metric for overall muscular strength and physical function in adult populations (59, 60). The evaluation will adhere to the standardized protocol established by the American Society of Hand Therapists (ASHT) (61). Participants will be positioned with the shoulder in a neutral alignment, the elbow flexed at 90 degrees, the forearm in a neutral orientation, and the wrist set between 0 and 30 degrees of extension. A maximum of three attempts will be conducted with each hand in an alternating sequence, incorporating rest intervals of no less than 30 s between trials. The maximum recorded value (kg) will be utilized for further analyses. Results will be analyzed utilizing age- and sex-specific normative reference values pertinent to the Chilean population (62).

##### Lower limb strength

4.14.2.2

The five-times sit-to-stand test (5 × STS) will be utilized to assess lower limb muscle strength, as it is a validated and commonly employed functional measure of lower extremity strength (63). The assessment measures the duration (in seconds) taken by participants to stand up from and sit back down in a standard chair (height 43–45 cm) for five consecutive repetitions, with arms crossed over the chest to eliminate assistance (64).

